### Setting, criteria

#### Participants

The research focuses on students aged between 16 and 19 years from a secondary school in Budapest (Óbudai High School). We plan a pilot study from the results of the first 60 schoolchildren to be able to make a power analysis and an effect size.

The main trial is planned to involve 330–360 students. If necessary, we will consider to involve more high schools to participate.

A written informed consent provided from the participants and their parents is needed to participate in the study before any trial procedures occur (see Appendix 3 for a sample of the written informed consent form). The text of the consent will be sent out before the study to participants and the written formats will be collected by instructors on-site, at the beginning of trainings. In addition, students will need to fill out a brief questionnaire about their basic characteristics and future educational motivation (gender, age, prior participation in BLS course, plans about future specialisation, etc). The participation in the study will be voluntary. Students can indicate any time their withdrawal from the trial.

Student eligibility for the trial must comply with all the criteria listed and reviewed in Table 2.

**Table 2 t0010:** Inclusion and exclusion criteria (BLS: Basic Life Support).

*Inclusion criteria*	*Exclusion criteria*
High school teenagers participating in the education of Óbudai High School, Budapest	No written informed consent provided by the student and/or parent. Unwilling to participate on site
Written informed consent received from participants and their parents to participate in the study	Any injury or health issue influencing the efficacy of BLS performance

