#### Randomisation

Students will be simply randomised in two groups by randomly dividing the groups. Participants randomised to **Instructor Group** will take part in a 90-minute-long BLS training and get a feedback based on the own experience of the instructor. Students randomised to **Software Group** will also take part in a 90-minute-long BLS training, but they will receive feedback by a real-time software-based feedback system (Ambu Man model C Manikin, Ambu A/S, Ballerup, Danish Kingdom, and InnoMed CardioAid-1 Trainer AED, Innomed Inc., Budapest, Hungary). There will be four BLS training occasions for the 360 students organized during school time with the help of teachers. Students applying for the first two occasions of the trainings will be randomised to Instructor Group and students applying to the last two occasions will be randomised to Software Group. Two authors (CsM and EZ) will be responsible for the randomisation and students’ enrolment to the study. All students will receive a code that will be added to a Microsoft Excel spreadsheet (Microsoft Corporation, Redmond, WA) with the name and grouping information of the students. To secure students’ anonymity, only the codes will be used during the evaluation and data process. Due to the nature of the study and intervention students and instructors will know which group they belong to during the trainings. Skill retention assessment with an observational checklist will be performed at the end of the training, two months later and six months later by our instructors to evaluate short- and long-term BLS skill retention. All data regarding the students’ performance will be added to another Microsoft Excel spreadsheet. The instructors will be blinded during skill retention assessment and will not be aware of student grouping. The assessor instructors will be independent from the instructors educating during the trainings. Fig. 1 summarizes the flow of the trial.

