#### CPR skills assessment and data collection

Students’ characteristics and skill retention assessments results (BLS Skill Scores) will be collected in a Microsoft Excel spreadsheet and compared between the Instructor Group and Software Group at each time points of the study, respectively. For the next step, the overall results of skill retention assessments will be evaluated and the results will be compared to assess the efficacy of the BLS education method. One of the authors (ÁPJ) will check the quality of data and will store them. Due to the nature of the study (manikin-based study investigating education methodology) data monitoring committee will not be set up. Only the authors will have access to the data. The participants can check their own results and have access to them for request. Results will be communicated via scientific publication with anonymised data. Moreover, public media presentations are planned with the written consent from participants and their parents.

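### Allocation is not concealed at entry: the training occasion fixes the arm before written consent is collected, and the two authors who randomise also enrol

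*Protocol article*

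**What the plan says.** All of this is in the protocol article.

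- **Roles (Randomisation).** Two authors "will be responsible for the randomisation and students" enrolment into the study.
- **Stated method (Randomisation).** "Students will be simply randomised in two groups by randomly dividing the groups". The Design section calls the trial individually randomised, 1:1.
- **Operating rule (Randomisation).** There are four training occasions for 360 students. The arm follows from the occasion: "Students applying for the first two occasions of the trainings will be randomised to Instructor Group". The remaining two occasions are tied in the same way to the other arm.
- **Consent (Participants).** The text is sent out beforehand, but the "written formats will be collected by instructors on-site, at the beginning of trainings".
- **Exclusion (Participants, Table 2).** One listed reason is "Unwilling to participate on site".
- **Blinding (Randomisation).** It covers the assessors when skills are assessed. Students and training instructors know the group during training.
- **Analysis (Statistical analysis).** The groups are compared by chi-square, t or Mann-Whitney tests. No covariate adjustment of that comparison is named.

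**The concern.** Concealment means that nobody who can affect whether a student enters, or on which occasion, knows the arm before entry is final. Here the arm can be read from the occasion, and entry is completed only when the consent form is handed over at that occasion. A student may prefer a date for reasons related to ability or interest, a teacher may steer a class to one session, and a student may decline on site knowing which feedback method is on offer. The two authors who enrol know the arm as well.

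At stake is the protection that randomisation should give the primary comparison, the skill score at the end of training. The investigators collect prior BLS training and career plans and make professional motivation a secondary analysis, so they consider such factors relevant. If these differ between arms because of how students entered, the difference passes straight into an unadjusted comparison.

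**Working it through.** **Step 1: order of events as written.**

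1. A student applies for one of four occasions (Randomisation).
2. The occasion determines the arm: the first two give Instructor, the last two give Software (Randomisation).
3. At the start of that occasion the instructors collect the written form (Participants).
4. A student unwilling on site is excluded (Table 2).

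The arm is fixed at step 2 and entry is completed at steps 3 and 4. Under this rule anyone who knows the occasion predicts the arm with 100% certainty, against 50% under a concealed simple 1:1 allocation.

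**Step 2: does a stated safeguard close the gap?** Assessor blinding acts after training and addresses biased scoring, not selection at entry. Codes are used in evaluation and data processing and protect anonymity, not allocation. The article describes no other step between enrolment and assignment.

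**Step 3: what the shared roles add.** One pair of people doing both tasks does not prove that concealment is absent, since they could use a concealed mechanism. The occasion rule is what settles the matter. The shared roles count because, if the occasion rule were replaced by a true random list and nothing else changed, the people enrolling would still be in charge of that list.

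**Step 4: illustration of size.** The plan gives no figure to reproduce. Inputs:

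- 180 students per arm: 360 / 2, from the target sample size and the 1:1 ratio.
- Effect of a prior BLS course on the score: 0.5 SD (assumed).
- Difference between arms in the share with a prior course: 10 or 20 percentage points (assumed).
- Independent students, no true effect, two-sided 5% test, normal approximation.

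SE of the arm difference = sqrt(2/180) = 0.105 SD.

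Bias = prevalence difference × 0.5 SD. The rejection rate is P(Z > 1.96 − d) + P(Z < −1.96 − d), with d = bias / SE.

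| Imbalance | Bias | d | Rejection rate |
|---|---|---|---|
| 0 points | 0 | 0 | 5% |
| 10 points | 0.10 × 0.5 = 0.05 SD | 0.05 / 0.105 = 0.47 | 7.6% |
| 20 points | 0.20 × 0.5 = 0.10 SD | 0.10 / 0.105 = 0.95 | about 16% |

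These rates show how the bias scales. They do not predict what will happen in this trial.

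**The case against.** The strongest reply is that the role sentence alone says little. It names who is responsible for two tasks, and how a sequence is concealed is detail that an article may leave to the full protocol. That would stand if the article said no more. But it also fixes the occasion rule and the timing of consent, and a fuller document cannot add concealment without contradicting them.

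A second reply is that this is only a consequence of allocation by occasion. In part it is: that rule is the larger defect, and splitting the roles would not cure it. The remedy still has separate parts, because a true random list held by the people who enrol, or consent taken after assignment, would leave entry open.

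A reader might infer three stronger things that the documents do not support:

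- **That the two authors decide which arm a student gets.** Students apply for occasions, teachers help to organise them, and instructors collect consent. No discretion of the two authors over placement is described.
- **That the enrolling authors work from a list prepared in advance.** The spreadsheet holds the code "with the name and grouping information of the students", but it may be a record made after assignment. The later sentence limiting data access to the authors appears with the characteristics and assessment results and says nothing about a sequence before entry.
- **That anyone steers students by prior training or career plans.** These come from the student questionnaire, and nothing shows that the two authors have the answers when they enrol.

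It is also fair to object that the 0.5 SD effect and the imbalances are assumed, and that the milder case moves the error rate only from 5% to 7.6%. That stands.

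**Conclusion.** The point holds. As written, the arm is known before entry is complete, to the enrolling authors and potentially to students, teachers and the instructors collecting consent. This is a stated arrangement, not missing detail. It allows selection into or out of an arm, mainly through choice of occasion and refusal on site, and the planned unadjusted tests do not correct for it.

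Whether such selection will occur, in which direction and how strongly, cannot be told from the article. The false-positive rate of about 8% to 16% depends entirely on the assumed 0.5 SD effect, a 10- to 20-point imbalance and independent students. The conclusion rests on the occasion rule together with the consent timing, with the shared roles as a contributing weakness. The change should be made, since it is cheap and the claim of individual randomisation depends on it.

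**What to change.** Three passages should change together: the role sentence and the occasion rule in Randomisation, and the consent timing in Participants.

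1. Collect written consent and the questionnaire before any student's arm is known.
2. Close the list of consented student codes. Do this separately for the pilot of the first 60 students and for any school added later, so that those options remain available.
3. Have an existing author who takes no part in enrolment, teaching or assessment draw the 1:1 allocation from the codes alone, without names, and release it only after the list is closed.
4. Assign students to training occasions according to the drawn arm, so that the occasion follows from the allocation and not the reverse.

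Reassigning the roles without steps 1 and 4 would leave every arm predictable.

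The cost is earlier collection of consent, some scheduling work with the school, and no late additions to a closed list. No new staff are needed.

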**Fig. 1 f0005:**
[figure not shown]
Trial flow diagram.

### Trial interventions

#### Instructors

Instructors teaching CPR at our department either hold an ERC Certificate or are trained based on the ERC Educational Guidelines and Principles.^6^

In order to make BLS trainings and data recording unified, the Instructors participated on an internal pre-training standardised and tailored to the high school BLS education.

The teacher to student ratio will be 1:6 and in some exceptional cases no more than 1:7 during BLS practices.

#### BLS training

Students will receive a 90-minute long BLS training according to the actual ERC Guideline. Peyton’s Four-Step Approach will be the teaching method that will be used during BLS training. It contains four important steps: 1. real-time instructor demonstration of BLS on a manikin without any explanations; 2. repeated instructor demonstration with detailed explanation followed by students’ questions if any; 3. instructor demonstration based on a volunteer or selected student’s instructions; 4. student’s demonstration with instructor’s help if needed.^6^

After the four-step demonstration students will work in pairs to practice BLS. They will have to solve simple scenarios and have enough time to practice the whole algorithm. All participants in the **Instructor Group** will receive feedback separately based on the instructor’s own experience by following the key points of the checklist. Beside the presence of important steps in BLS, the instructor will observe and give feedback based on experience by strengthening the key points of the checklist (see Appendix 4). A software-based real-time system will be used in **Software Group**. It will give feedback about the qualities of the chest compression (depth, frequency, chest release, rhythm, etc.) and ventilation. In addition, the instructor will give feedback regarding the presence of the most important steps of BLS.

The key messages during the training will be the proper initiation of chain of survival by checking environmental safety, checking the victim’s response to voice and tactile stimuli, opening the airways, checking the breathing, asking for help and performing high-quality chest compressions combined with rescue breathing in 30:2 ratio during BLS.^15^ The components of high quality chest compressions and rescue breaths are detailed in Appendix 4.

#### Primary outcome

BLS skill scores will be measured immediately at the end of the training based on a checklist reviewed above (see Appendix 4). The assessment will be performed by one or two instructors and the Innomed CardioAid-1 Trainer AED system.

#### Secondary outcome

BLS skill scores will be measured two and six months after the educational session, based on the procedure reviewed above. Skill retention assessment occasions will be organized in the school with the help of teachers in the same way as the training, during school time.

The influence of professional motivation (planning a profession in health care or not) on BLS performance will also be analysed.

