## Methods

### Design

The trial is an anonymous, interventional, prospective longitudinal, assessor blinded, individually randomised, parallel 1:1 grouped trial to determine and compare the efficiency of the two teaching methods: feedback given by the instructor or by a software and CPR-sensor module on the efficacy and quality of chest compressions during the course. This protocol has been written in concordance with the SPIRIT guidelines (Table 1 and Appendix 1).^14^

**Table 1 t0005:** Trial registration data set (BLS: Basic Life Support).

Data category	Information
Registry	ClinicalTrials.gov ID: NCT06016153
Date of registration	08/2023
Human Subjects Review	Board Status: Approved Approval Number: 160/2023 Board Name: Semmelweis University Regional and Institutional Committee of Science and Research Ethics Board Affiliation: Semmelweis University Email: [contact] Address: [name]
Primary sponsor	Semmelweis University This funding source had no role in the design of this study and will not have any role during its execution, analyses, interpretation of the data, or decision to submit results.
Secondary sponsor	none
Central Contact Person	[name] [contact]
Central Contact Backup	[name] PhD [contact]
Study Officials	[name] PhD Study Principal Investigator, Semmelweis University
Public Title	The Efficacy of Basic Life Support Education Among Teenagers
Scientific Title	The Investigation of the Efficacy of Basic Life Support Education Among High School Students
Countries of recruitment	Hungary
Health condition(s) or problem(s) studied	The quality of Basic Life Support
Intervetion(s)	BLS training, feedback given by the instructor or a CPR analyser software
Key inclusion criteria	• High school teenagers (aged 16–19 years) participating in the education of Óbudai High School, Budapest • Written informed consent received from participants and their parents to participate in the study
Key exclusion criteria	• Missing written informed consent provided by the student or parent • Any injury or health issue influencing the efficacy of BLS skill
Study type	• Study Type: Interventional • Interventional Study Model: Parallel Assignment • Number of Arms: 2 • Masking: Single (Outcomes Assessor) • Allocation: Randomized
Date of first enrolment	December 2023
Target sample size	360
Recruitment status	Recruiting
Primary outcome(s)	Results of the assessment at the end of the training

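### In-school six-month assessments after a December 2023 start leave almost no calendar slack, and because arm follows calendar order, retention interval and missing data can differ between arms

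*Protocol article*

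**What the plan says.** - **Start.** Table 1 (Design) gives the date of first enrolment as "December 2023".
- **Population.** Table 1 admits "High school teenagers (aged 16–19 years) participating in the education of Óbudai High School, Budapest". Neither Table 1 nor Table 2 (Participants) asks that a student will still attend the school six months after training.
- **Follow-up.** Under Secondary outcome, "BLS skill scores will be measured two and six months after the educational session", and these assessments are to be "organized in the school with the help of teachers in the same way as the training, during school time".
- **Arm and calendar.** Under Randomisation, "There will be four BLS training occasions for the 360 students organized during school time with the help of teachers". Whoever signs up for occasion 1 or 2 goes to the Instructor arm. For occasions 3 and 4 the rule reads: "students applying to the last two occasions will be randomised to Software Group".
- **Analysis.** Under CPR skills assessment and data collection, the arms are compared at each time point. Under Statistical analysis, the three assessments within a group are compared by a Friedman test. Up to 5% missing data are dropped; above 5%, multiple imputation is used.
- **Skill decay.** The Introduction places the loss of BLS skills between three and twelve months after training.

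The article gives no term dates, no dates or spacing for the four occasions, no distribution by school year, and no provision for leavers or for visits that fall due in a school break.

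**The concern.** Three stated features interact: a December start, follow-up tied to the school day, and arms filled in calendar order. The first two push the six-month visit to the end of the school year or beyond. The third means that whatever happens at that boundary is not shared evenly by design. A student whose date falls in the break is either missed or seen after the summer, at a longer retention interval. A student who has left may not be seen at all.

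Long-term retention is a stated aim, and the six-month result is listed as a key secondary outcome. If one arm is assessed later than the other, at a time when the protocol itself expects skills to be falling, the between-arm difference mixes teaching method with elapsed time. If one arm loses more leavers, the students compared also differ in age and school year.

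**Working it through.** The protocol has no figure of its own to reproduce here, so the check is date arithmetic.

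**Inputs from the protocol.** First enrolment December 2023; four occasions for 360 students, so 360 / 4 = 90 per occasion and 180 per arm if occasions are equal; occasions 1–2 Instructor, 3–4 Software; visit due at training date + 6 months; 5% missing-data threshold.

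**Assumptions, since the protocol is silent.** First training on 1 or 15 December; equal spacing of 0, 1, 7, 14 or 30 days; last school day 31 May, 15 June, 21 June or 30 June 2024; school resumes on 1 September. Weekends and a winter break are ignored.

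**Step 1: earliest due date.** 1 December + 6 months = 1 June; 15 December + 6 months = 15 June. January and February trainings fall due in July and August. March + 6 months = September, which is in term again.

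**Step 2: visits due after the last school day.** Over the whole grid, the counts (Instructor / Software) run from 0/0 to 180/180. Examples:

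| First training | Spacing | Last school day | Instructor | Software |
|---|---|---|---|---|
| 1 Dec | 0–1 day | 15, 21 or 30 June | 0 | 0 |
| 1 Dec | 7 days | 15 or 21 June | 0 | 90 |
| 1 Dec | 14 days | 15 or 21 June | 0 | 180 |
| 15 Dec | 7 days | 21 June | 90 | 180 |
| either | any | 31 May | 180 | 180 |

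**Step 3: allow for September.** For students who stay at the school, a date after 1 September is in term again, and this changes the pattern.
- Monthly spacing from 15 December gives due dates of 15 June, 14 July, 13 August and 14 September. With term ending 21 June, occasions 2 and 3 fall in the break: 90/90.
- Occasion 1 on 1 December, occasion 2 in mid-January and occasions 3–4 in March give due dates of 1 June, mid-July and September: 90/0.

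For continuing students the direction therefore depends on dates that the article does not state.

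**Step 4: leavers.** A student who leaves on date L is out of reach if training date + 6 months > L. That condition is met by later trainings whenever it is met by earlier ones. If final-year students are similarly represented at each occasion, losses of leavers fall equally on the arms or more on the Software Group.

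**Step 5: retention interval.** Take two-weekly occasions from 1 December (1, 15 and 29 December, 12 January) and term ending 21 June. The Instructor occasions fall due on 1 and 15 June and can be seen at six months. The Software occasions fall due on 29 June and 12 July. Seen on 1 September, they are at 8 months 3 days and 7 months 20 days.

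**Step 6: missing data.** 0.05 × 360 = 18. Losing more than 18 students at six months passes the threshold for imputation.

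**The case against.** The strongest reply is that nothing in the article shows a conflict. Four occasions close together in early December, with term running to mid or late June, put every six-month date in term. Session calendars and visit windows are usually left to a full protocol, the flow diagram and appendices are not shown, and the primary outcome is untouched. Imputation can also draw on immediate and two-month scores and age.

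Much of this stands. The absence of a visit window is not in itself a finding, and the zero-conflict case is real on term dates alone. Three stronger readings that a reader might infer are not supported:

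- **That many visits will fall after term.** The result runs from none to all, depending on unstated dates.
- **That a quarter to a third of students will be lost.** If the final year were one of three or four year groups, 25–33% of 360 is 90–120 students. That share is assumed, and the figure counts every final-year student at every occasion as lost, so it is an upper bound and not an estimate.
- **That the Software Group is always worse off.** Step 3 gives an equal and a reversed case for continuing students.

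What the reply does not remove is that the start month, the in-school rule and the calendar-ordered arms are stated choices, not omitted detail. Together they leave almost no room for slippage, and any slippage is tied to arm. Imputation does not cure this, because few six-month values from leavers would be available to inform it. The arm imbalance does stem from the allocation scheme, which raises wider questions; correcting that scheme would remove the imbalance but not the problem of dates falling in the break.

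**Conclusion.** The point holds as a risk built into the stated schedule, not as a demonstrated loss. What is certain is that no six-month date precedes June 2024 and that the arms are separated in calendar time. Given a break from about mid or late June to September, trainings from about late December through February fall due in the break, while those in early December or from March can be on time. The size is indeterminate: 0 to 180 of 180 visits per arm due after the last school day over the assumed range.

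The consequence is confined to the six-month between-arm comparison and the three-time-point Friedman test. In the Friedman test, a six-month score taken late, or imputed for a leaver, distorts the apparent course of retention. The matter should be corrected because the remedy is specific and cheap relative to a six-month assessment that cannot be recovered once a student has left.

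**What to change.** 1. **Balance the calendar.** Train both arms at each occasion, or at least in the same weeks, with students allocated individually within the occasion. This matches the individually randomised design that the protocol claims, and it balances the retention interval and leaver losses whatever the school calendar turns out to be.
2. **Schedule backwards from follow-up.** Set each remaining occasion so that its two- and six-month dates both fall in term while the participants still attend. Early-autumn occasions, for example, reach six months around March.
3. **State what happens to leavers.** If final-year students are trained too late for an in-school six-month visit, keep them for the immediate and two-month outcomes and define the six-month comparison among students still attending. Identify that group from school year at enrolment, so that membership does not depend on anything that happens after allocation.

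**Cost.** Running both methods at the same occasion needs separate practice groups and instructors briefed for each. Rescheduling may delay occasions not yet held by months. The six-month result would then apply to continuing students only, on a smaller number. Excluding final-year students altogether is possible but gives up their earlier outcomes, and the case for it is debatable.
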